### Explanation for the choice of comparators {6b}

The eM2M intervention is designed to progressively increase exercise duration to meet the U.S. recommended exercise guidelines of 150 min of moderate-intensity physical activity every week [30]. The intervention utilizes movement routines choreographed to music to target four fitness components: range of motion, muscular strength, cardiorespiratory endurance, and balance. Table 1 highlights the general structure of the eM2M intervention. The study aims to examine the effects of the 12-week eM2M intervention by comparing *eM2M* participants with *WC* participants.

**Table 1 Tab1:** eM2M intervention structure

Training component\week		1	2	3	4	5	6	7	8	9	10	11	12
		Duration (minute)											
**Warm up** **(Range of motion)**	**Upper body**	5	5	5	5	5	5	5	5	5	5	5	5
	**Lower body**	5	5	5	5	5	5	5	5	5	5	5	5
**Upper extremity muscle strength**		5	5	5	5	5	5	5	5	5	5	5	5
**Cardiorespiratory fitness**		10	10	15	15	20	20	25	25	30	30	30	30
**Lower extremity muscle strength**		5	5	5	5	5	5	0	0	0	0	0	0
**Balance**	**Static**	5	3	3	2	2	0	0	0	0	0	0	0
	**Dynamic**	0	2	2	3	3	5	5	5	0	0	0	0
**Cool down/mindfulness**		5	5	5	5	5	5	5	5	5	5	5	5
**Total minutes**		**40**	**40**	**45**	**45**	**50**	**50**	**50**	**50**	**50**	**50**	**50**	**50**

### Intervention description {11a}

The eM2M intervention consists of three sessions per week for a total of 36 sessions over 12 weeks. The intervention provides three different programs based upon participants’ functional mobility, which are classified into: Group I (seated exercise only), Group II (seated and standing exercise with or without support while standing), and Group III (exercise for right and left side of the body).

#### Utilization of the Zoom platform and technology

All participants will be mailed a laptop after they officially enroll in the study. The laptop will be used for completing the teleassessments with study staff as well as participating in the intervention. The laptop will have a preinstalled shortcut on its desktop for easy access to the eM2M sessions. The shortcut will direct *eM2M* participants to the password-protected intervention website that will prompt them to input vital signs and answer questions on rating of perceived exertion (RPE), pain, and fatigue when they login 15 min prior to each eM2M session. The vital signs include resting blood pressure, heart rate, and peripheral oxygen saturation that are measured with a portable blood pressure monitor and a pulse oximeter mailed with the laptop. If participants’ vital signs are within safe range for exercise (blood pressure ≤ 180/110 mmHg; heart rate ≤ 100 bpm; oxygen saturation ≥ 90%), participants will then be directed to the Zoom platform for the eM2M session. If a vital sign is not within a safe range, participants will be redirected to a webpage that informs them to rest for a few minutes before attemping to login again. If upon a second attempt a vital sign is still not within a safe range, participants will be instructed to call study staff and be recommended to not join the class that day.

All eM2M sessions will be delivered by a trained M2M instructor from the Telehealth Center at Lakeshore Foundation, Birmingham, AL. The sessions will be supported by a research assistant, who will facilitate the instructor and participants with technical difficulties and ensure delivery quality of the eM2M sessions. At the beginning of each session, the instructor will ask all participants to set their Zoom screens to gallery view so everyone can talk and interact with each other. Before starting the first movement routine, the research assistant will spotlight the instructor’s video to ensure participants are able to easily view and follow the instructor’s movements. The research assistant will also mute participants’ microphones to prevent background noise from interfereing with the session. Participants will be instructed to raise their hand if they encounter any issues during the session, and the research assistant will transfer the participants to a Zoom breakout room to resolve the issues. Toward the end of the session, the instructor will ask all participants to change back to gallery view for a cool-down and mindfulness routine so everyone can see each other in one screen. Once the session concludes the intervention website will redirect participants to input their vital signs and complete the same questions that they completed before the session.

#### Components of the eM2M intervention

The eM2M intervention is highly structured to ensure strong fidelity between instructors. Each session consist of 7 to 8 movement routines accompanied with music. Every routine incorporates combinations of various movement patterns and sequences that target one of the four fitness components described below and can be adapted to the participants’ functional mobility level.

#### Range of motion component

Each session starts with two 5-min range of motion routines that serve as the warm-up and focus on upper and lower extremity joint movements performed in a seated position. The upper range of motion routine targets upper limb movements including (1) neck flexion, extension, lateral flexion, and rotation; (2) shoulder extension, lateral/frontal/dorsal extension, flexion, adduction, horizontal adduction, abduction, horizontal abduction, circumduction, and rotation; (3) shoulder girdle elevation and depression; (4) elbow extension and flexion; (5) wrist extension, flexion, and rotation; (6) hand extension and flexion; and (7) torso lateral/frontal/dorsal extension and rotation. The lower range of motion routine targets lower limb movements including (1) hip extension, flexion, adduction, horizontal adduction, abduction, horizontal abduction, and rotation; (2) knee extension and flexion; (3) ankle extension, flexion, and rotation; and (4) toes extension and flexion. The movement tempo ranges from 12 to 60 beats per minute (bpm).

#### Muscle strengthening component

The muscle strengthening component consists of one 5-min seated routine that targets upper extremity muscle groups including biceps, triceps, deltoid, trapezius/rhomboids, pectorals, erector spinae, rectus abdominus, and obliques as well as one 5-min standing routine that target lower extremity muscle groups including quadriceps, hamstrings, gastrocnemius/soleus, and tibialis anterior. The routines are adapted for Group I participants, where the upper extremity strength routine focuses on the shoulder, chest, upper back, and arm muscles and the lower extremity strength routine focuses on the abdominal and lower back muscles. All *eM2M* participants receive a pair of 2-lb wrist weights mailed to them after randomization that are used to perform this routine. The movement tempo ranges from 40 to 60 bpm.

#### Cardiorespiratory fitness component

The cardiorespiratory fitness component consists of two routines that are performed at movement tempo that ranges from 100 to 180 bpm. The routines are structured with a series of movement combinations and can be performed seated or standing with or without support. The component begins with 10 min at week 1, progress to 30 min at week 9, and maintain 30 min for remaining weeks 10–12. Participants are asked to rate their RPE on a 0–10 Borg scale [31, 32] at the end of each cardiorespiratory fitness routine.

#### Balance component

The balance component consists of a 5-min routine that targets static and dynamic balance. This component begins with a static balance routine at week 1 and progresses to a dynamic balance-focused routine at week 8. The routine is adapted for Group I participants, which involves sitting stability, trunk rotation, and weight shifting with arms and upper body reaching in different directions.

#### Cool down/mindfulness component

The cool down/mindfulness component focuses on breathing and mindfulness where the instructor and participants come together while forming a virtual, imaginary circle. The instructor then delivers a mindfulness quote and ask participants to share their thoughts at the end of each session.

#### *Participant safety*

Before starting the intervention, study staff will confirm with the participants about their emergency contact information and instruct them to notify their emergency contacts about the intervention schedule. In the event of an emergency during the eM2M session, the research assistant will place the participant in a breakout room and confirm severity of the emergency. Should the emergency deem that medical help is necessary, study staff will first contact the participant’s emergency contact and will call 911 if the emergency contact cannot be reached.

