### Plans to give access to the full protocol, participant-level data, and statistical code {31c}

This paper provides the overall study protocol. Readers should contact the authors if interested in other data or documentation of the study.

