### Oversight and monitoring

#### Composition of the coordinating centre and trial steering committee {5d}

The study is a single-center trial. All study activities are performed and coordinated under the UAB/Lakeshore Research Collaborative. The day to day support for the study is provided by the following:
Scientific director: supervise the implementation and fidelity of the study protocol and intervention delivery.Project coorindator: coordinate all apsects of the study and manage its regulatory requirements.Rercuiment coordinator: recruit, screen, and obtain medical clearance for potential participants and support participant communication throughout the study period.Research assistants: perform day to day study tasks including study visit scheduling, equipment shipping, intervention preparation and monitoring, and participant communication.Study physician: review and approve medical clearance prior to participant enrollment as well as review adverse events.

The scientific director, the project coordinator, the recruitment coordinator, and research assistants communicate about the study on a daily basis. The project coordinator, recruitment coordinator, and research assistants meet weekly to go over project activities and study milestones.

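### Every in-session emergency needing medical help goes to the emergency contact before 911, with no exception for a life-threatening event

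*Protocol article*

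**What the plan says.** The emergency procedure is in the protocol article under Participant safety. Before the intervention starts, staff check each participant's emergency contact details and ask the participant to tell the contact when the sessions take place. If an emergency arises during a session, "the research assistant will place the participant in a breakout room and confirm severity of the emergency". The calls that follow depend on one condition, worded as "Should the emergency deem that medical help is necessary". When that condition is met, the order is fixed as follows: "study staff will first contact the participant’s emergency contact and will call 911 if the emergency contact cannot be reached".

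Three other places bear on the point:

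- Utilization of the Zoom platform and technology describes the vital-sign check before class. After a second out-of-range reading, "participants will be instructed to call study staff and be recommended to not join the class that day". On staffing, the same section says "The sessions will be supported by a research assistant".
- Composition of the coordinating centre and trial steering committee {5d} gives the physician's role: "Study physician: review and approve medical clearance prior to participant enrollment as well as review adverse events".
- Intervention description {11a} sets the schedule at "three sessions per week for a total of 36 sessions over 12 weeks".

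**The concern.** The text fixes an order of calls and applies it to every event that needs medical help. A sprain and a cardiac arrest take the same route: a layperson first, and 911 only if that person does not answer. For a collapse, a suspected stroke or a participant who stops responding, that is the wrong default.

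The setting makes the order matter. Participants exercise at home, and their qualifying diagnoses include stroke, brain injury, spinal cord injury and Parkinson's disease. The cardiorespiratory part of a session rises to 30 minutes (Table 1). The protocol's own adverse-event categories include falls and cardiovascular episodes. The article does not say that the contact must be in the home, nearby or available during sessions. What is at stake is the time before emergency services are called, not the validity of the trial's results.

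**Working it through.** No figure in the protocol is in dispute, so the check is a reading of the text: follow the stated procedure along each branch, then look for any other provision that changes it.

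**Following the procedure**

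1. The research assistant moves the participant to a breakout room and checks severity.
2. The stated result of that check is yes or no: medical help is needed or it is not. No higher tier is defined.
3. If the answer is yes, staff call the emergency contact. Two outcomes are possible:
   - *Contact not reached.* Staff then call 911, so at least one call comes before it.
   - *Contact reached.* No 911 call by staff is stated, and the text does not say what staff do next.

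In neither outcome is 911 the first call.

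**Looking for an override**

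| Section of the protocol article | What it governs | Changes the order of calls? |
|---|---|---|
| Eligibility criteria | Physician clearance; exclusion for contraindications to exercise | No; acts before enrolment |
| Utilization of the Zoom platform and technology, vital signs | Entry to the class | No; acts before the session |
| Utilization of the Zoom platform and technology, raised hand and breakout room | Issues that a participant signals during class | No; and an unresponsive person cannot signal |
| Composition of the coordinating centre and trial steering committee {5d} | Study physician: clearance and adverse-event review | No live emergency role is given |
| Adverse event reporting and harms {22} | Classification and reporting | No; acts after the event |

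The number 911 appears only under Participant safety.

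**Exposure**

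The order applies to 3 sessions per week × 12 weeks = 36 sessions per intervention participant. This counts the occasions on which the rule is in force; it does not count emergencies. The documents give no rate of in-session emergencies and no response times, so no expected number of events and no delay in minutes can be derived.

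**The case against.** The strongest reply is that this is a condensed journal article, and escalation tiers are the kind of detail that normally sits in an operating manual. The access statement ({31c}) says "This paper provides the overall study protocol", but it then tells readers to ask the authors for other documentation, so the article need not be the complete emergency procedure. This part stands: an unseen manual may contain an exception, and the access statement cannot be used to rule one out. The concern does not need it to. The article does not leave the order of calls open; it states one. A manual that sent life-threatening events straight to 911 would contradict the published text, which would then need correcting.

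A second reply is that the severity check implies judgement, and that nothing forbids staff from calling 911 at once. That is so, but the written instruction points the other way, and an assistant trained on it would be following the protocol by ringing the contact first.

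Third, contacts are not called cold: their details are confirmed and they are to be told the schedule. A contact who answers may summon help or be close by. This is a fair reason to keep the contact-first order for lesser events. It does not justify that order when minutes matter, because both calls can be made together.

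Fourth, clearance, exclusions and vital-sign limits make a serious event less likely. They do, but they leave the order of calls unchanged when one occurs.

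Last, the research assistant who would act also handles technical problems, muting and breakout rooms for the class, so parallel calls may stretch one person. This is a practical point for the fix, taken up there.

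**Conclusion.** The concern holds. The protocol states a single order of calls for every in-session emergency needing medical help, with the emergency contact ahead of 911 and no stated exception for a life-threatening event or an unresponsive participant. Nothing elsewhere in the article overrides it.

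The size can be given only in terms of procedure: at least one call before 911 if the contact does not answer, and no stated 911 call by staff if the contact does. No event count or length of delay is claimed. The conclusion rests on the published text being the instruction that staff follow; if a manual already provides a direct route to 911, only the article's wording needs correction.

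The point should be fixed because the possible harm is serious and the remedy is cheap. It does not touch randomization, outcomes or analysis.

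**What to change.** Replace the final sentence of Participant safety with wording such as:

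> If the participant is unresponsive or the event is judged life-threatening (for example collapse, chest pain, suspected stroke, or a fall with loss of consciousness), study staff will call 911, or the emergency service for the participant's location, at once and notify the emergency contact in parallel. For less severe events that need medical help, study staff may call the emergency contact first, will call 911 if the contact is not reached at the first attempt or cannot assist on site, and will stay connected until help is confirmed.

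If an operating manual already contains such a tier, bring the protocol text into line with it.

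The cost is one sentence replaced by two, brief retraining, and some 911 calls that prove unnecessary. An instructor and a research assistant already take part in the sessions, so the change should not need new staff. The documents do not show how the two would divide the work in an emergency, so the retraining should settle who calls 911, who calls the contact and who looks after the rest of the class.

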### Criteria for discontinuing or modifying allocated interventions {11b}

There are no criteria for discontinuing or modifying allocated Intervention when requested by participants. Participants may choose to stop the intervention or withdraw from the study for any reason, including being assigned to a study arm that is not a preference.

### Strategies to improve adherence to interventions {11c}

The eM2M intervention is underpinned by four Social Cognitive Theory constructs: self-efficacy, self-regulation, outcome expectations, and social support [33]. Self-efficacy is targeted through (1) *mastery experience*: begin with lower exercise intensity and movement complexity and progress to higher exercise intensity and movement complexity across the intervention, to ensure that participants are challenged in a progressive manner; (2) *verbal persuasion*: motivate and encourage participants during class through verbal positive reinforcement; and (3) *emotional/physiological states*: ask participants to rate their RPE as well as pain and fatigue level at the beginning and end of each eM2M session to increase awareness of emotional and physiological states. Self-regulation and outcome expectations are addressed by asking participants to set monthly exercise goals and discuss expectations they have about exercise. In addition, the eM2M instructors will explain targeted outcomes to participants at the beginning of each routine. Social support is addressed by having group classes where participants with similar functional mobility levels are exercising together and by giving participants time at the beginning and end of each class to talk and interact with each other. The purpose of having gallery view on the Zoom platform at the beginning and end of each session is to facilitate the group interaction and social support. In addition, email or text reminders will be sent to participants a day before the intervention starts and one hour prior to each eM2M session.

### Relevant concomitant care permitted or prohibited during the trial {11d}

Not applicable, no concomitant care or interventions are prohibited during the trial.

### Provisions for post-trial care {30}

Not applicable, no provisions for post-trial care are included in the study.

### Outcomes {12}

Primary and secondary outcomes include a set of physical assessments and self-report questionnaires and will be assessed at baseline and post 12-week intervention via the Zoom platform (teleassessments [34]) and REDCap electronic questionnaires. Assessors will be blinded to participant assignment, and allocation of the arm assignment will not be done until baseline testing is completed. The outcome measures included in this study were developed and validated in previous literature with adequate to excellent reliability. The primary outcomes include changes in cardiorespiratory fitness measured with resting heart rate [35] and the heart rate recovery test [36, 37] as well as muscle strength assessed with hand-held dynamometer [38–40] at post 12-week intervention. The secondary outcomes include changes in lower extremity function assessed with the Short Physical Performance Battery [41] and the Timed Up and Go tests [42–44], health-related quality of life measured using the NIH PROMIS 10 Global Health Items [45], social participation measured using the NIH PROMIS Ability to Participate in Social Roles and Activities Short Form 8a [45], and physical activity measured using the Godin Leisure Time Exercise Questionnaire [46–54] at post 12-week intervention. Table 2 summarizes all outcome measures and the corresponding data collection time points.

**Table 2 Tab2:** Outcome measures of the M2M study

Role	Variables	Outcome measures	Collection time points
**Primary outcomes**	Cardiorespiratory fitness	Resting heart rate [35] Heart rate recovery test [36, 37]	Baseline and 12 weeks
	Muscle strength	Hand-held dynamometer [38–40]	Baseline and 12 weeks
**Secondary outcomes**	Lower extremity function	Short physical performance battery [41] Timed up and go [42–44]	Baseline and 12 weeks
	Health-related quality of life	NIH PROMIS 10 Global Health Items [45]	Baseline and 12 weeks
	Social participation	NIH PROMIS Ability to Participate in Social Roles and Activities Short Form 8a [45]	Baseline and 12 weeks
	Physical activity	Godin Leisure Time Exercise Questionnaire [46–54]	Baseline and 12 weeks
**Mediators**	Program adherence	Percentage of # of attended eM2M sessions	12-week intervention period
	Group cohesion	Physical Activity Group Environment Questionnaire [55–57]	12 weeks
	Instructor support	Perceived Autonomy Support Scale for Exercise Settings [57, 58]	12 weeks
	Exercise self-efficacy	Exercise Self-efficacy Scale [59]	Baseline and 12 weeks
	Exercise self-regulation	Exercise Goal-setting Scale [60]	Baseline and 12 weeks
	Outcome expectations for exercise	Multidimensional Outcome Expectations for Exercise Scale [61]	Baseline and 12 weeks
	Social support for exercise	Social Provisions Scale [62]	Baseline and 12 weeks
**Moderators**	Functional mobility	Short Physical Performance Battery [41]	Baseline
	Disability type	Demographics and Health History Questionnaire	Baseline
**Covariates**	Barriers in physical activity	Barriers in Physical Activity Questionnaire [63]	Baseline

In addition, after participants complete the eM2M intervention, they will be asked to participate in semi-structured interviews via Zoom. The interviews will be conducted in a group format (the same group of participants that underwent the intervention together). The interviews will include questions that probe participants’ perceived impact of eM2M on their health and function, as well as their experience exercising with other participants with similar functional levels who have different disabilities. The interviews will be audio-recorded, transcribed, and analyzed using a latent thematic analysis approach (underpinned by interpretivism).

